#### Sample size {14}

Sample size calculation was performed via PASS version 15 software before trial initiation based on the following: (1) no relevant current data for the effect of FMT on hypertension; (2) a clinically significant improvement of a decrease in office SBP at least 5 mmHg associated with reduction in stroke (14%), cardiovascular disease (9%), and mortality (7%) [32]; (3) meta-analysis of the effectiveness of probiotics on hypertension based on randomized controlled clinical trials that revealed a reduction of SBP of 3.56 mmHg (95% CI, 6.46 to 0.66) [33]. Assuming a true SBP difference between the “FMT capsule group” and “placebo group” with a mean of 5 mmHg and a standard deviation of 8.6 mmHg for SBP change per arm, a sample size of 96 grade one hypertensive patients yields > 80% statistical power to demonstrate a > 5 mmHg difference between arms at a 1-sided alpha level of 0.025. Given the potential for premature withdrawal or failure before the primary end point data were collected, a 20% rate of loss-of-follow-up was considered, resulting in 120 participants with grade one hypertension according to the “2010 Chinese Guidelines for Prevention and Treatment of Hypertension” [28]. Participants were recruited and randomized 1:1 to receive FMT by capsule or placebo capsules.

#### Recruitment {15}

Eligible participants will be screened at the hypertension outpatient clinic of the implementation centers according to the eligibility criteria for the trial. Advertisements for the study will utilize onsite posters and multiple media platforms.

### Assignment of interventions: allocation

#### Sequence generation {16a}

Randomization allocation sequencing was performed at a 1:1 ratio in blocks of four and stratified by center, by an independent statistician via the SAS 9.4 software (SAS Institute, Cary NC, USA) and incorporated into a central computerized randomization system that was developed and managed by the Medical Research & Biometrics Center, National Center for Cardiovascular Diseases, Fuwai Hospital Chinese Academy of Medical Sciences.

#### Concealment mechanism {16b}

Only the staff from the Medical Research & Biometrics Center who will generate the random codes and an independent staff member from the responsible center (Fuwai Hospital) will maintain the overall random codes that will be incorporated into the Electronic Data Capture System (EDC system) and will maintain the sealed envelopes for each participant.

#### Implementation {16c}

Patient care providers and investigators from implementation centers will log in to the EDC system, enter the system login page, select the center, fill in the password, and enter the randomization information page. After inputting the name of the implementation center, qualified screening code, initials of participants’ name, age, sex, and other relevant information; passing the system check for information correction; and clicking the “submit for confirmation” button, the randomization date, qualified random number; and allocated arm of participants will be obtained. At this time, participants are enrolled in this study.

The eligible participants will be randomly divided into two arms: the “FMT capsule” group and the “placebo capsule” group which will receive FMT capsules or placebo capsules, respectively, three times in the outpatient department on day 1, day 7, and day 14 after the trial initiation. The random numbers are labeled on the package for capsules in accordance with the GCP. The first administration (day 1) will be commenced after randomization with medication compliance/adherence, adverse events, and treatment for comorbid diseases assessed and recorded via investigators and/or patient care providers.

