### Trial design {8}

This study is an investigator-initiated, multicenter, randomized, blinded, placebo-controlled clinical trial with a 3-month duration.

Assuming a true SBP difference between the “FMT capsule group” and “placebo group” with a mean of 5 mmHg and a standard deviation of 8.6 mmHg for SBP change per arm, a sample size of 96 grade one hypertensive patients yields > 80% statistical power to demonstrate a > 5 mmHg difference between arms at a 1-sided alpha level of 0.025. Given premature withdrawal or failure potentials before the primary end point data were collected, a 20% rate of loss-of-follow-up was calculated, resulting in the recruitment target of 120 participants with grade one hypertension who met the eligibility criteria. The participants will be randomized 1:1 to receive FMT via capsule or placebo capsules. The experimental group will then be offered three separate “FMT capsule” treatments (day 1, day 7, day 14), and the control group will then be offered three separate “placebo capsules” (day 1, day 7, day 14). In addition to the comprehensive examination before the intervention period and at the end of the trial, participants in both arms will be followed up at day 7, day 14, day 30, day 60, and day 90 to undergo an assessment of their clinical BP and other clinical indicators. Adverse events and treatment for other accompanying diseases will also be recorded at each visit, and fecal and blood samples will be collected before the trial and at each visit for future metagenomic and metabolomic profiling analysis. All staff involved in the clinical assessments, statistical analysis, and/or randomization of participants will be blinded.

The protocol report refers to the SPIRIT reporting guidelines [27].

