### Assignment of interventions: blinding

#### Who will be blinded {17a}

Study participants and all personnel, including investigators, patient care providers, and/or data analysts who recruit and follow-up participants and collect and analyze data, will be blinded. The packaged intervention capsules and sealed emergency envelopes for each participant will be prepared by independent staff from the responsible center not involved in the study. The sealed envelopes are maintained at the responsible center for disclosure of arm allocation when necessary.

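### The randomization procedure gives site staff the participant's allocated arm, which contradicts the protocol's own blinding and code-holding rules

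*Protocol article*

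**What the plan says.** Implementation {16c} describes the randomization step. The users are site staff: "Patient care providers and investigators from implementation centers will log in to the EDC system". After they enter the participant's details and confirm, "the randomization date, qualified random number; and allocated arm of participants will be obtained". The arm is listed as an item separate from the random number. The next paragraph of that section names the arms in clear, as "two arms: the “FMT capsule” group and the “placebo capsule” group", and describes no masked label. It also says that the capsule packages carry the random number.

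Four other statements bear on this:
- Trial design {8}: "All staff involved in the clinical assessments, statistical analysis, and/or randomization of participants will be blinded".
- The blinding section {17a} lists those kept unaware of allocation, data handlers among them: "Study participants and all personnel, including investigators, patient care providers, and/or data analysts who recruit and follow-up participants".
- Concealment mechanism {16b} names the holders of the codes: "Only the staff from the Medical Research & Biometrics Center who will generate the random codes and an independent staff member from the responsible center".
- Sections {17a} and {17b} keep sealed envelopes at the responsible center and allow unblinding in a medical emergency, with reason, date, place and signatures recorded.

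**The concern.** The roles that receive the arm in {16c} are the roles that {8} and {17a} declare blinded. The oversight section {5d} gives one category of site staff the tasks of screening, recruitment, follow-up and adverse event handling. Office BP is recorded at the follow-up visits, and its systolic change to day 30 is the primary outcome. Under {11b} and {11d}, investigators or physicians also judge discontinuation and the need for antihypertensive drugs.

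If those staff know the arm, choice of readings, advice, drug decisions and attribution of adverse events could differ between arms. A difference of a few mmHg from such sources could not be separated from an FMT effect, against a design effect of only 5 mmHg. The trial's description as blinded would also not be accurate.

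**Working it through.** **1. The statements side by side**

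| Question | Implementation {16c} | Elsewhere in the article |
|---|---|---|
| Who operates the randomization page? | Site care providers and investigators | Staff involved in randomization are blinded ({8}) |
| What do they receive? | Date, random number and allocated arm | Recruiting, follow-up and data-collecting staff are blinded ({17a}) |
| Who holds the codes? | Not addressed | Biometrics staff and one independent person only ({16b}) |
| How is an arm disclosed? | At every randomization | Sealed envelope when needed ({17a}); documented emergency unblinding ({17b}) |

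The arm stands beside the random number as a further item, so it is hard to read as another name for that number. The arm is not needed for dispensing, because the packs carry the random number. If the site login already showed the arm, the envelopes and the unblinding record would have no function. The contradiction is textual and needs no arithmetic.

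**2. The design figures, reproduced**

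Inputs from Sample size {14}: difference 5 mmHg, SD 8.6 mmHg per arm, one-sided alpha 0.025, 96 evaluable (48 per arm), 20% loss.
- SE of the difference = 8.6 × √(2/48) = 1.755 mmHg.
- Noncentrality = 5/1.755 = 2.848; with 94 degrees of freedom, power = 80.5%, as claimed (> 80%).
- 96/(1 − 0.20) = 120, as claimed.

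**3. What a differential bias would do (illustration)**

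The bias sizes are assumptions; the article gives none. With no true effect and a bias b favoring FMT, the rejection probability is that of a noncentral t with 94 degrees of freedom, noncentrality b/1.755 and critical value 1.986.

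| Assumed bias b | b/1.755 | One-sided error (noncentral t) | Normal approximation |
|---|---|---|---|
| 0 mmHg | 0 | 2.5% | 2.5% |
| 1 mmHg | 0.570 | 8.1% | 8.2% |
| 2 mmHg | 1.139 | 20.3% | 20.6% |
| 3 mmHg | 1.709 | 39.4% | 40.1% |

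These use a two-sample comparison, as in the sample size section. The planned covariance analysis adjusts for baseline SBP and center; if that shrinks the residual SD, the same bias would inflate the error somewhat more.

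**The case against.** The strongest defense is that {16c} is loosely worded. It uses a passive and does not say that a site screen shows FMT or placebo in clear. Everything around it describes masked allocation: restricted code holders, packs labeled by number, independently prepared capsules and envelopes, documented emergency unblinding, and a blinding audit report at database lock in Data management {19}. This stands as a reason not to conclude that unblinding occurred. It does not remove the contradiction, because the procedure as published hands over the arm and nothing in the article says it is masked.

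A reader might also infer that the person who sees the arm takes the BP reading. The article does not say so: the visit descriptions state only that BP is recorded, and {5d} groups staff by category. The exclusion criteria refer to electronic BP measurement, which limits reader bias, though not selection of readings, co-intervention or adverse event attribution.

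Finally, a reader might infer that allocation was predictable, since the list was "performed at a 1:1 ratio in blocks of four and stratified by center". With all earlier arms known, enumeration of the six possible blocks leaves 33.3% of assignments determined and 70.8% correctly guessable. That requires the arm to have been displayed, the block size to have been known at the sites, and prior allocations at the center to have been tracked. The article establishes none of these. Recruitment of all 120 was complete by 16 September 2021 (Trial status), so advice on block size would change nothing.

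**Conclusion.** The contradiction is real and should be corrected: {16c} conflicts with {8}, {16b}, {17a} and the emergency route in {17b}. Followed as written, it would unblind the category of site staff who recruit, follow participants up and handle adverse events.

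The consequence for the primary endpoint is conditional. It depends on the arm actually having been shown, and on staff who saw it having influenced readings or care. The article shows neither. The error rates of about 8%, 20% and 39% rest on assumed biases of 1, 2 and 3 mmHg with 48 per arm and SD 8.6. They show how sensitive the test is and do not estimate any bias in this trial. The documents do not support a claim that the primary result is biased or that allocations were foreseen. The sample size and alpha are unaffected.

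**What to change.** 1. Reconcile {16c} with {8}, {16b} and {17a}: state that site users receive only the randomization date and the random or pack number, and that the arm stays with the code holders named in {16b}.
2. Keep the arm field masked for site, data-management and analyst logins until database lock.
3. Establish what the site screen showed during the completed recruitment. If it showed the arm, document who saw it and whether they recorded BP, and report this wherever the trial is described as blinded. The blinding audit report in {19} is a natural place for the record.
4. In that case, name the day-30 24-h ambulatory SBP comparison as the check on the office result before the data are unblinded. It is already collected and already a secondary outcome, and {20c} leaves the analysis open to finalization until database lock. It is less observer-dependent, but differential co-intervention would affect it too.

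The cost is a wording correction with the ethics approval that {25} requires for protocol changes, a check of EDC permissions, and a query to the sites. No participants, visits or measurements are added.

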### Assignment of interventions: blinding

#### Who will be blinded {17a}

Study participants and all personnel, including investigators, patient care providers, and/or data analysts who recruit and follow-up participants and collect and analyze data, will be blinded. The packaged intervention capsules and sealed emergency envelopes for each participant will be prepared by independent staff from the responsible center not involved in the study. The sealed envelopes are maintained at the responsible center for disclosure of arm allocation when necessary.

#### Procedure for unblinding if needed {17b}

If medical emergency events occur, unblinding can be performed if necessary via the responsible investigation team under the supervision of the principal investigator. The reason, date, location of unblinding, and signatures of investigators will be recorded in detail. All participants will be followed up until the close-out visits unless the withdrawal criteria are met.

### Data collection and management

#### Plans for assessment and collection of outcomes {18a}

All outcomes will be evaluated at seven time points, including baseline, the first intervention day, and 7 days, 14 days, 30 days, 60 days, and 90 days after intervention initiation. In addition to the kick-off meeting on February 26, 2021, all staff involved in the study were trained on a detailed study protocol, participant recruitment and informed consent, clinical assessment, sample collection and storage, and data collection utilizing printed CRFs and EDC systems.

#### The week prior to enrollment (− 1~0 week)

The following procedures will be completed:
Written informed consent will be obtained from the participants for the study, and the screening questionnaire will be completed.Office blood pressure and heart rate will be recorded.Previous history, current and prior treatment, and other documented eligibility factors will be recorded.Personal information such as height, weight, and waist circumference will be recorded.Examinations including 24-h ABPM, electrocardiography, routine blood tests, blood biochemical tests, routine urine tests, urine microalbumin, creatinine, and arterial stiffness assessments (PWV, ABI) will be performed.Participant eligibility will be reconfirmed according to the inclusion and exclusion criteria.The baseline case report form (CRF) with printed CRF and EDC system will be completed.Fecal and blood samples will be collected.The appointment for the randomization visit will be made (within a week after screening).

#### Randomization (day 0)

Participants will be randomly assigned to receive the first capsule treatment (day 1), and a dietary history will be collected before treatment.

#### Treatment period (day 1, day 7, day 14)

The eligible subjects will be randomly divided into two arms, in which the “FMT capsule” group and the “placebo capsule” group will receive FMT via capsules or placebo capsules, respectively, three times in the outpatient clinics on day 1, day 7, and day 14 after the trial initiation. At each visit, medication adherence, adverse events, treatment for comorbid diseases, and dietary history will also be assessed and recorded.

#### Follow-up visits (day 7, day 14, day 30, day 60)

Office blood pressure and heart rate will be recorded, and on day 30, 24-h ABPM will be performed.Any reasons for discontinuing intervention will be recorded.Adverse events, participant adherence to treatment regimens, and changes in combined medication for comorbid diseases and nonstudy therapy will be recorded.Dietary history will be recorded.Blood and fecal samples will be collected.The follow-up CRFs will be completed with printed CRF and EDC systems.An appointment for the next follow-up visit will be made.

#### Final visit (day 90)

Participants will undergo a comprehensive examination to evaluate the efficacy of FMT for hypertension treatment, including physical examination, blood pressure, heart rate, 24-h ABPM, routine blood tests, routine urine tests, blood biochemical tests, urine microalbuminuria protein, creatinine, electrocardiography, and arterial stiffness assessments (ABIs, PWVs). In addition, dietary history, adverse events, and combined medications for comorbid disease will be recorded, and all CRFs will be reviewed. Additionally, effective colonization and durability of intestinal flora in hypertensive recipients after oral administration of “FMT capsules” or “placebo capsules” and the underlying mechanism of BP change and the fecal microbiota will be analyzed via metagenomic and metabolomic profiling analysis.

### Plans to promote participant retention and complete follow-up {18b}

All enrolled participants will receive a comprehensive health evaluation via a professional physician and will receive FMT capsules or placebo capsules for free. During the average follow-up of 3 months, participants will receive consultation from professionals, medication guidance, and follow-up services for free. To assist in travel costs and other expenses to take part in the study, subsidies will be provided for each participant per visit. In terms of participants refusing to follow the allocated intervention algorithm or experiencing adverse events, follow-up in reference to the evaluation plan will continue. The reason for withdrawal (and degree of withdrawal) will be recorded for all participants who withdraw from the study or who are not thoroughly followed up. If participants withdraw, clinical treatment and other rights and interests of patients will not be affected.

### Data management {19}

Data collection will be performed via the printed CRF, and then data will be entered into the Electronic Data Capture (EDC) system (http://47.107.145.115/fmtEDC/) developed by the National Center for Cardiovascular Diseases, enabling repeated confirmation from the patient care providers and/or investigators from the implementation centers. All staff will be trained and e-mailed with accounts and passwords for using the EDC system with signed meeting summaries. The EDC system will automatically check the data format, rules, and range, which will then be rechecked manually. All printed CRF and examination results will be scanned and sent to the Collaborating Office with two staff independently reconfirming the accuracy of the data. Changes in data are allowed and tracked with reasons in the EDC system. Additionally, a third party is invited to supervise data quality. After completion of the study, the EDC database will turn to a locked state with the blinding audit report generated by the statistician and confirmed by the principal investigator, responsible data manager, and statistical analyst. Data will be kept for 5 years after study completion.

### Confidentiality {27}

In terms of protection of participant confidentiality, personal information of participants, including name, address, contact, and personal ID numbers, will be kept within investigation centers, and access by any third party will be prohibited. Regarding data collection (i.e., metagenomic profiling, metabolomic profiling, clinical information, and examination results), all personal identifiers will be removed with alternatives such as unique screening code and randomization code used.

### Plans for collection, laboratory evaluation, and storage of biological specimens for genetic or molecular analysis in this trial/future use {33}

Except for routine clinical laboratory tests for blood and urine samples (will not be stored) as described above, study blood (10 ml) and fecal (5 g) samples will be collected at baseline and at each visit. Blood samples will be centrifuged immediately with supernatants and blood cells collected separately. These samples will be stored in − 80 °C freezers and delivered to the responsible center via dry ice for further metagenomic and metabolomic profiling analysis. Other experiments, such as specific bacteria isolated from fecal samples, may be developed to address the scientific questions of the study.

## Statistical methods

### Statistical methods for primary and secondary outcomes {20a}

All primary analyses for end points will be based on the intent-to-treat principal, including all randomized patients received at least a capsule, regardless of adherence. For primary endpoint analysis, analysis of covariance adjusting for baseline SBP and center will be performed. In terms of baseline data and secondary outcomes, categorical variables will be described as frequencies (percentages, %), with differences between the arms evaluated through the Cohran-Mantel-Haensel chi-square test or Fisher’s exact test as appropriate, with center effect adjustment. Continuous variables are presented as the mean (standard deviation (SD)) or median (interquartile range (IQR)), with *t* tests or Wilcoxon tests performed as appropriate. Assessment of interventions according to the change in continuous data will be performed using mixed-effect models or the analysis of covariance. All statistical tests of clinical metadata will be conducted using the SAS®9.4 software or the R software (version 4.0.2). A significance level of one-sided *p* < 0.025 will be utilized for primary endpoint analysis, and a significant *p* value for other statistical analyses is defined as a 2-sided *p* < 0.05.

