### Eligibility criteria {10}

The following are the inclusion criteria:
Age 18~60 yearsEstablished diagnosis of grade one hypertension (initial diagnosis or no use of antihypertensive drugs within a month): 140 mmHg ≤ office SBP < 160 mmHg and/or 90 ≤ office DBP < 100 mmHg from three measurements on different days without any antihypertensive medications, according to the “2010 Chinese Guidelines for Prevention and Treatment of Hypertension” [28].Participants who provide written informed consent after receiving a thorough explanation.

The following are the exclusion criteria:
Antibiotic or probiotic usage within one month before the studyParticipation in other clinical trials related to hypertension currently or within the last 3 monthsAntihypertensive medication usage currently or within the last monthDiagnosis of secondary hypertensionSevere hepatic or renal diseases (over 3-fold elevation of alanine transaminase, elevated serum creatinine over 2.5 mg/dl [221 μmol/L], estimated glomerular filtration rate less than 30 mL/min/1.73 m^2^, or end-stage kidney dysfunction requiring dialysis)History of stroke, including hemorrhagic stroke and large artery atherosclerotic cerebral infarction (LAACI) but not transient ischemic attack (TIA) or lacunar infarctionHistory of hospitalization within the last 6 months due to myocardial infarction, history of coronary revascularization including percutaneous transluminal coronary intervention (PCI) or coronary artery bypass grafting (CABG) within the last year, anticipated PCI or CABG surgery in the following 12 monthsSustained atrial fibrillation or arrhythmias at recruitment disturbing the electronic BP measurementNYHA class III–IV heart failure, hospitalization for chronic heart failure exacerbation within the last 6 monthsSevere valvular diseases: potential for surgery or percutaneous valve replacement within the study periodDilated cardiomyopathy; hypertrophic cardiomyopathy, rheumatic cardiac disease, congenital cardiac diseaseOther severe diseases influencing the entry or survival of participants, such as malignant tumors or acquired immune deficiency syndromeCognitive impairment or severe neuropsychiatric comorbidities, making individuals incapable of providing their own informed consentParticipants preparing for or currently experiencing pregnancy and/or lactationOther conditions deeming individuals inappropriate for recruitment according to the investigators

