### Outcomes {12}

Our primary hypothesis is a BP-lowering effect of gut microbiota restoration via FMT compared to the effects observed in the placebo group in grade one hypertensive patients. Accordingly, the primary outcome is defined as the change in office systolic blood pressure (SBP) level from baseline to the one-month follow-up (day 30).

Other indicators related to BP evaluation, safety concerns, and potential mechanism exploration will be assessed as the main secondary outcomes and include the following:

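### The primary ANCOVA leaves out baseline 24-h ambulatory SBP, which is measured before randomization: a missed and possibly small gain in precision, not an error

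*Protocol article*

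**What the plan says.** The section on statistical methods for primary and secondary outcomes {20a} fixes the covariates of the primary model: "analysis of covariance adjusting for baseline SBP and center will be performed". The primary outcome (Outcomes {12}) is the change in office SBP from baseline to day 30. Center is also the stratification factor of the randomization (Sequence generation {16a}).

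The visit plan for the week before enrollment lists "Examinations including 24-h ABPM, electrocardiography, routine blood tests" among the procedures, and Table 1 marks 24-h ABPM in the screening column, ahead of allocation. Outcomes {12} uses ambulatory pressure only as a secondary outcome, as change to day 30 and day 90. Nowhere is the baseline recording named as a covariate.

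Sample size {14} assumes a difference "with a mean of 5 mmHg and a standard deviation of 8.6 mmHg for SBP change per arm" and states that "a sample size of 96 grade one hypertensive patients yields > 80% statistical power" at one-sided 0.025. It claims no gain from covariate adjustment.

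Section {20c} plans multiple imputation for the primary endpoint and no handling of missing data for secondary endpoints. It also says that the final protocol and statistical analysis will be settled before the database is locked.

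**The concern.** Office SBP varies from visit to visit, so one office value, or a mean of a few, is an imperfect measure of a patient's usual pressure. A 24-h mean rests on many readings. Two patients with the same baseline office SBP but different ambulatory means would be expected to differ in office SBP at day 30, the one with the higher ambulatory mean tending to be higher. That difference stays in the residual of the planned model although it was known before randomization.

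A prognostic baseline covariate, fixed in advance, narrows the confidence interval for the treatment effect without introducing bias and without one more patient. This matters here because the design has little margin over 80% power, and because Trial status reports that all 120 participants have been recruited. The analysis model is one of the few places where precision can still be gained.

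**Working it through.** **Inputs from the documents.** Difference 5 mmHg, SD of change 8.6 mmHg per arm, 96 evaluable patients at 1:1 (48 per arm), one-sided alpha 0.025, 20% loss (Sample size {14}).

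**Input not in the documents.** The partial correlation r between baseline 24-h SBP and the day-30 change in office SBP, given baseline office SBP, center and arm. Assumed range: 0.1 to 0.4.

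**1. The plan's own figure.** SE = 8.6 × √(2/48) = 1.755 mmHg. The noncentral t with 94 degrees of freedom gives power of 80.5%. With 47 per arm it gives 79.6%, so 48 per arm is the smallest size above 80%. 96/0.8 = 120. Both stated figures reproduce. Taking off 8 degrees of freedom (six for seven centers and one for each of two baseline covariates) gives 80.4%, a change of less than 0.1 point.

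**2. Adding the covariate.** The residual SD becomes 8.6 × √(1 − r²). This step takes 8.6 as the residual SD of the planned model. Results with 48 per arm:

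| Assumed r | Residual SD | SE | Power | Equivalent evaluable N = 96/(1 − r²) |
|---|---|---|---|---|
| 0 | 8.60 | 1.755 | 80.5% | 96 |
| 0.1 | 8.56 | 1.747 | 80.9% | 97 |
| 0.2 | 8.43 | 1.720 | 82.0% | 100 |
| 0.3 | 8.20 | 1.675 | 84.0% | 105 |
| 0.4 | 7.88 | 1.609 | 86.8% | 114 |

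The gain runs from 0.4 to 6.3 percentage points. The residual variance falls by r², that is, by 1% to 16%.

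**3. If the planned covariates already help.** The 8.6 is described as "a standard deviation of 8.6 mmHg for SBP change per arm", so it need not be the ANCOVA residual SD. Suppose baseline SBP and center together correlate 0.3 with the change (assumed). The starting SD is then 8.6 × √(1 − 0.09) = 8.20, and the planned model already has 84.0% power. Adding ambulatory SBP with r = 0.1 to 0.4 takes it to between 84.4% and 89.7%, a gain of 0.4 to 5.7 points.

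**4. What values of r are plausible.** An illustrative simulation assumed a between-patient SD of true SBP of 8 to 12 mmHg, an office visit error SD of 6 to 8 mmHg, and a correlation of 0.6 to 0.9 between ambulatory and true office SBP. None of these values is in the documents. It gave r of about 0.20 to 0.45 if baseline office SBP is a single reading, and 0.09 to 0.28 if it is a three-day mean. The article does not say which of the two baseline SBP is. At 0.09 to 0.28, the method of step 2 gives power of 80.8% to 83.6%.

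**5. Does the entry window matter?** In the same simulation, restricting baseline office SBP to 140–160 mmHg rather than 125–160 mmHg cut its SD from about 8–9 to about 5–5.5 mmHg. The partial correlation of ambulatory SBP was essentially unchanged (for example, 0.35 under both windows in one single-reading setting).

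**The case against.** The strongest reply is that nothing here is wrong. The model adjusts for the baseline value of the outcome and for the stratification factor, which is standard. The power claim holds without any further covariate. The article condenses a fuller protocol, and the final analysis is still to be settled before database lock. All of this stands, and it limits the point to an optional improvement.

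The reply also holds on size. The gain depends on a correlation that the documents do not contain. With a three-day mean as baseline it could be close to nothing, and the planned adjustment may already have lifted power above 80.5%.

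A reader might infer more: that the entry criterion squeezes baseline office SBP into a 20 mmHg band and so makes it a poor covariate, while ambulatory SBP keeps its full range. The documents do not support this. The criterion reads "140 mmHg ≤ office SBP < 160 mmHg and/or 90 ≤ office DBP < 100 mmHg from three measurements on different days", so a patient can enter on diastolic pressure with SBP below 140. Narrowing the office range also does not change what ambulatory SBP adds given office SBP (step 5). And selecting on office pressure narrows ambulatory pressure too, because the two are correlated. Nor does the model rest on office SBP alone, since center is in it as well. The argument rests on measurement error in office pressure and on the recording already being scheduled.

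The change is also not quite free. The planned multiple imputation covers the primary endpoint; no stated rule covers a missing baseline covariate.

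**Conclusion.** The point stands as a missed precision gain. The primary model names its covariates and omits a plausible prognostic measurement that is scheduled before randomization. The planned ANCOVA is valid and unbiased, and the claim of more than 80% power is correct.

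Over the assumed range of r, the gain is between negligible and about 6 points of power. It rests on three assumptions: r between 0.1 and 0.4, 8.6 mmHg as the residual SD, and 48 evaluable patients per arm. It should not be read as a finding that the trial is underpowered or that its primary test is flawed.

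**What to change.** Before unblinding, and within the step that section {20c} already foresees before database lock:

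- Add baseline mean 24-h SBP as a linear covariate to the primary ANCOVA, beside baseline office SBP and center.
- Include the same variable in the multiple-imputation model for the primary endpoint.
- State a rule for missing or invalid baseline recordings, for example imputing the covariate without regard to arm.
- Keep the model with baseline SBP and center as a supporting analysis.

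The cost is a few lines of text, one degree of freedom, and the added rule for missing recordings. The gain may turn out negligible; if so, almost nothing is lost.
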